### Control intervention

The control group will receive Treatment As Usual only. This will be monitored via questionnaire, and a weekly client contact sheet completed with each school.

### Outcome measurements

#### Student outcomes

Participants will be assessed prior to delivery of the intervention (baseline), immediately post-intervention (10 weeks) and 12 weeks later. The research assistant will administer each of the following measures at each time point, with the exception of the evaluation questionnaire, which is only administered post-intervention. All assessments will be conducted at school.

The primary outcome is reduced suicidal ideation at post-intervention and follow-up, measured by the Suicidal Ideation Questionnaire (SIQ), a 30-item self-report measure designed to assess suicidal ideation in adolescents. It has been validated with clinical and non-clinical populations and shown to have high levels of internal consistency and test-retest reliability, and high levels of construct and criterion validity [41,42].

Other outcomes to be measured include:

• Suicidal acts - using a series of specifically-designed questions.

• Depressive symptoms - using the clinician-rated Children's Depression Rating Scale-Revised (CDRS-R) [43], and the Reynolds Adolescent Depression Scale-2 (RADS-2) [44]. The CDRS-R is a semi-structured interview schedule originally designed for use with children but also successfully used with adolescents. It rates depressive symptoms across 17 domains including difficulties with schoolwork, social withdrawal, appetite and sleep disturbance, fatigue, guilt and suicidal ideation. The first 14 items are rated on the basis of responses to interview questions from the young person, and are rated for the past two weeks and currently. The remaining three symptom areas (depressed facial affect, listless speech and hypoactivity) are rated by the clinician on the basis of the participant's non-verbal behaviour. Each symptom is graded on a 5 or 7-point scale with increasing scores indicating increasing severity of symptoms. The total score, or CDRS-R score, is the sum of all 17-item scores and the instrument has a range of 17-113. This scale is used widely, has adequate internal reliability, good test-retest reliability, good to excellent inter-rater reliability and is sensitive to treatment effects [43,45]. The RADS-2 is 10-item brief screening measure for the assessment of current depressive symptoms in adolescents aged between 11 and 20. It can be used in clinical or non-clinical populations and takes around 2-3 minutes to complete. Items assess mood or reduced affect, loneliness, social withdrawal, sadness, self-harm, self-reproach, self-worth, anger/irritability, loss of interest and helplessness. Participants are asked to rate how often they experience each item on a 4-point Likert scale ranging from ‘almost never’ to ‘most of the time’. Responses are rated from 1-4, giving a possible total score range of 10-40 points, with higher scores indicating greater symptom severity. The instrument includes one reverse-scored item that is worded in a positive manner, so that reversing the individual’s score represents greater depression. A cut-off score of 26 on this measure indicates clinically significant symptomatology. The RADS-2 has demonstrated strong internal consistency and a moderately high level of test-retest reliability among school students. It has also demonstrated strong evidence of criterion validity when assessed against both clinical interview and self report measures of depression, and strong construct and clinical validity [44,46].

• Hopelessness will be measured using the Beck Hopelessness Scale [47]. This is a self-report scale consisting of 20 true or false items, 9 or which are keyed ‘false’ and 11 are keyed ‘true’. For every statement, each response is assigned a score of 0 or 1, and the total ‘hopelessness score’ was the sum of the scores on the individual items. Thus, the possible range of scores was from 0 to 20, with a higher score indicating a greater degree of hopelessness. A cut-off score of 9 on the scale has been found to be predictive of eventual suicide among clinical samples [48]. This scale has been found to have a high degree of internal consistency and good test-retest reliability and good construct and concurrent validity.

• Anxiety will be measured using the Multidimensional Anxiety Scale for Children [49]. This is a 39-item self-report instrument that assesses the major aspects of anxiety in young people. Items are distributed across four dimensions: physical symptoms, harm avoidance, social anxiety and panic. Participants are asked think about how they have been feeling recently and to rate each item on a 4-point scale of 0-3 ranging from this is ‘never true about me’ to this is ‘often true about me’. Scores are derived from totals on each subscale together with those from a total anxiety scale, an anxiety disorders index and an inconsistency scale. Detailed instructions on scoring and interpretation are provided in the user manual. The MASC has shown adequate internal consistency and satisfactory test-retest reliability. It also has strong discriminant validity and moderate construct validity [49].

• Problem-solving skills will be assessed using the Negative Problem-Oriented Questionnaire [50]. This is a 12-item self-report measure that assesses negative problem orientation. Participants are asked to rate their responses on a 5-point scale with responses ranging from 1 – ‘not at all true of me’ to 5 – ‘extremely true of me’. The measure is unifactorial with no inverted questions. A higher score indicates a greater degree of negative beliefs concerning one’s problems and problem-solving ability. The scale has demonstrated excellent internal consistency, good test–retest reliability at five weeks, and both convergent and discriminant validity when measured against self-reported pessimism, depression, anxiety, and problem-solving ability.

• The Cognitive-behavioural Therapy Skills Questionnaire [51] will be used to test which components of the CBT appear to be most active. This 16-item scale measures the use of cognitive restructuring and behavioural activation skills i.e. changes in avoidance/behavioural control and changes in cognitive style. Respondents rank each item on a 5-point Likert scale from 1 (I don’t do this) to 5 (I always do this). It is a relatively new measure but it has been shown to be both reliable and valid.

• Distress will be measured using the abbreviated version of the Profile of Moods States (POMS) [52,53]. The POMS is a 14-item self-administered checklist measuring transient mood states. This measure has been used previously with adolescents for this purpose [54] and has been demonstrated to be sensitive to short-term change [52,53]. The POMS data can be used to produce the following six subscales: anger, depression, fatigue, tension, confusion and vigour. The score of each item ranges from 0-4. Each subscale is scored by adding up the scores of the related items and a higher score reflects greater presence of that item.

• At baseline, demographic information will be collected using a specifically designed questionnaire, and the first four subscales of the Comprehensive Assessment of At-risk Mental State (CAARMS) [55], to screen for psychosis. The CAARMS is a semi-structured clinician administered interview schedule that was specifically designed to assess for signs of psychosis in young people. It includes eight subscales that measure disorders of thought content; perceptual abnormalities; conceptual disorganisation; motor changes; concentration and attention; emotion and affect; subjectively impaired energy and impaired tolerance to normal stress. Scores for each subscale range from 0-6 with a higher score indicating greater likelihood of a psychotic disorder being present. It has been found to have good to excellent concurrent, discriminant and predictive validity and excellent inter-rater reliability.

To test for possible confounders the following will also be assessed:

• Treatment history - using a specifically developed questionnaire.

• Substance use, via the Substances and Choices Scale [56], which is a one-page self-report questionnaire designed for young people aged 13-18 years and takes about 5 minutes to complete. It has three sections. The first section records the number of occasions the young person has used a variety of substances in the last month. The second section measures both substance use related symptoms and substance related harm. Scoring this section yields the ‘SACS difficulties score’ from 0 to 20. This score can be used to screen or measure change through a treatment episode. The third section asks about tobacco use. It has been shown to demonstrate good reliability and validity.

• Help seeking via the General Help Seeking Scale [57]. The General Help Seeking Scale measures help-seeking intentions, appraising both formal and informal sources. Participants rate help-seeking intentions ranging from 1 (‘extremely unlikely’) to 7 (‘extremely likely’) for each help source option including ‘no one’. Higher scores indicate higher intentions.

Participant satisfaction and the extent to which they find the program acceptable will be measured using a specifically designed measure at post-intervention.

All outcome measures with the exception of the CDRS-R will be administered online. Research staff will receive training in the administration of the CDRS-R by one of the two clinical psychologists on the study team. All research staff will also be trained in the assessment of suicide risk.

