### Statistical analysis

#### Student outcomes

At each follow-up time point the general linear model will test for the treatment factor, i.e. compare the intervention and control groups for each outcome measure. Corresponding baseline values of each outcome measure will be used as the covariate. In addition, possible effect of site will be examined by introducing a school factor in the analysis. Multi-level modeling will be used to compare the two groups in terms of the trend over time for each outcome. Both the last observation carried forward and multiple imputation techniques will be considered if missing data are substantial. Interim analysis will be conducted twice yearly, or upon request to facilitate the safety monitoring of the project.

Adherence will be measured using data automatically collected by the system (e.g. number of times each participant logs onto the site, amount of time spent on the site, proportion of activities completed).

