### Effect size and statistical power

The primary outcome of interest is changes in suicidal ideation from baseline measured at 10 and 22 weeks. This will be measured by the SIQ. No previous studies have tested the effects of an Internet-based CBT intervention on suicidal ideation, however one previous study [59] has reported moderate to large effect sizes in terms of reduced suicidal ideation, for face-to-face CBT among young people. If we assume that alpha is set at 0.05 and power at 0.80, then a sample size of 58 is required for each of the two groups (total n = 116) to detect a medium effect size. This is based on using the general linear model to compare the intervention and control groups with the baseline values of an outcome measure as the covariate. It is assumed (conservatively) that the covariate would explain 10% of the variance in the dependent variable. Using data from the pilot study, the intra-cluster correlation corresponding to the schools is estimated to be 0.023, which in turn gives an estimate of 1.1 for the design effect. So in order to take account of the clustering effect of the schools, the sample size needs to be inflated to 128 (116 × 1.1).

A previous RCT conducted by the study team with a similar population had a dropout rate of 24% [60]. The proposed study differs in that the intervention will be delivered by school staff and all follow-up assessments will be conducted at school. It will also employ a shorter follow-up period, however we have estimated a dropout rate of 24% meaning that we need to recruit 169 students (128/0.76) into the study. We estimate that we can recruit about 6 students from each school, so we need to recruit 28 schools. Based on data obtained from a pilot study conducted prior to developing the RCT [39] we consider these figures to be feasible.

Every effort will be made to promote participant retention, including close liaison with school staff, maximum flexibility on the part of research staff conducting follow-up assessments, and by employing a number of methods to contact students for follow-up assessments. These will include contacting the participant via the school wellbeing coordinator in the first instance, but also by contacting them directly via phone or email and contacting them via their parents/guardians if necessary.

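### SIQ is primary at both 10 and 22 weeks with a test at each and no success rule, but the sample size covers a single test at 0.05 with power 0.80

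*Protocol article*

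**What the plan says.** Under Outcome measurements, Student outcomes, the article says: "The primary outcome is reduced suicidal ideation at post-intervention and follow-up, measured by the Suicidal Ideation Questionnaire (SIQ"). The section Effect size and statistical power repeats both visits: "The primary outcome of interest is changes in suicidal ideation from baseline measured at 10 and 22 weeks". Neither place ranks them.

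Under Statistical analysis, Student outcomes: "At each follow-up time point the general linear model will test for the treatment factor". Baseline values are the covariate, so SIQ receives two baseline-adjusted comparisons. The same paragraph adds: "Multi-level modeling will be used to compare the two groups in terms of the trend over time for each outcome".

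The sample size uses one significance level and one power: "If we assume that alpha is set at 0.05 and power at 0.80". The target is 58 per group ("total n = 116) to detect a medium effect size"), and the model is a single comparison: "This is based on using the general linear model to compare the intervention and control groups with the baseline values of an outcome measure". The baseline covariate is assumed to explain 10% of the variance. The total is then inflated by a design effect of 1.1 to 128, and for 24% dropout to 169.

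**The concern.** Two unranked primary visits, each with its own test, need a rule for what counts as success. The sample size has no room for that choice, because it is the size for one comparison at one visit. If the rule is left open until results are known, a positive primary claim could rest on whichever visit reached significance, at an error rate above the stated one. If both visits are needed, the chance of missing a real medium effect is nearer 30% than the planned 20%.

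**Working it through.** **Inputs.** From Effect size and statistical power: alpha 0.05, power 0.80, medium effect, covariate R² = 0.10, 58 per group, design effect 1.1, dropout 24%. Assumptions not in the article:
- Medium means d = 0.5, at both visits where two are considered.
- Tests are two-sided.
- Each visit is tested at 0.05. The article gives this level only once, as a sample-size input.
- The correlation r between the two test statistics lies between 0.24 and 0.7. The lower end follows if SIQ correlates equally across all three assessments: R² = 0.10 gives √0.10 = 0.316, and after baseline adjustment r = (0.316 − 0.10)/(1 − 0.10) = 0.24. The upper end is chosen to show the range.

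**Step 1: reproduce the plan's figure.** The residual SD is √0.9 = 0.949. The standard error with 58 per group is 0.949 × √(2/58) = 0.176, so the noncentrality is 0.5/0.176 = 2.84. The noncentral t with 113 degrees of freedom gives power 0.803, and 58 is the smallest n per group that reaches 0.80. The normal approximation gives 57. A one-sided test would need only 45, so the plan's figure is two-sided. Then 116 × 1.1 = 127.6, rounded up to 128, and 128/0.76 = 168.4, rounded up to 169. Every stated figure reproduces, for one test at one visit.

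**Step 2: either visit suffices.** Type I error = 1 − P(|Z₁| < 1.96 and |Z₂| < 1.96), with Z₁ and Z₂ bivariate normal with correlation r.

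**Step 3: both visits required.** With power 0.80 at each visit, joint power = Φ₂(0.842, 0.842; r). Type I error is at most 0.05, because both tests must reject.

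| r | Type I error, either visit | Power, both visits |
|---|---|---|
| 0.24 | 0.096 | 0.66 |
| 0.4 | 0.093 | 0.68 |
| 0.5 | 0.091 | 0.69 |
| 0.7 | 0.084 | 0.71 |

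The bounding case for type I error is two independent tests: 1 − 0.95² = 0.0975.

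**Step 4: sensitivity of the joint power.** The plan calls R² = 0.10 conservative. With equal SIQ correlation across the three assessments, d = 0.5, 58 per group and the normal approximation (which puts power for one visit at 0.81 rather than 0.80), joint power is:
- 0.68 at SIQ correlation 0.316 (R² = 0.10)
- 0.78 at 0.5 (R² = 0.25)
- 0.94 at 0.7 (R² = 0.49)

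The 66-71% therefore belongs to the plan's stated assumptions and rises if baseline SIQ is more prognostic.

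**Step 5: one deciding visit.** With one named visit, step 1 applies unchanged: alpha 0.05, power 0.80, and 58/116/128/169.

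**The case against.** The strongest reply is that a success rule and an order of testing are usual content of a statistical analysis plan. None is shown here, and this is a condensed article. On that view the gap is one of reporting. The natural reading of a primary outcome at one visit and another is also that both are required, which does not inflate type I error.

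Much of this stands. The article nowhere says that either visit suffices, so the 8-10% is conditional on that rule. The level of 0.05 per test is inferred. What remains is that the article itself fixes two primary visits, a test at each, and a sample size for one test. Those stated elements do not fit together without a rule. The both-required reading avoids the error inflation but not the loss of power.

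A reader might go further and infer three things that the documents do not support:
- **That the trend model is a third route to primary success.** The sample size is tied to the general linear model, the trend comparison is listed for every outcome, and nothing makes it decisive. Its time coding is not given either, so neither an error rate that includes it nor a criticism of a linear slope can be drawn from the text.
- **That the stated alpha and power fit no reading of the plan.** They hold together once one visit decides, or for the first visit in a fixed order.
- **That 10 weeks must be the deciding visit.** The article lists both visits equally.

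**Conclusion.** The concern holds as a mismatch between a two-visit primary outcome and a one-test sample size, with no stated success rule. Over an assumed test correlation of 0.24 to 0.7, an either-visit rule at 0.05 each gives type I error of about 8-10% against a stated 5%. A both-visits rule keeps type I error within 5% but gives power of about 66-71% against a stated 80%. The power figure assumes d = 0.5 at both visits and a covariate R² of 10%, and improves with a stronger baseline covariate. The sample-size arithmetic itself is correct for a single test.

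**What to change.** Before unblinding, name one visit's baseline-adjusted arm comparison on SIQ as the single primary test at two-sided 0.05. It can be the general linear model the trial was sized for, or the same contrast from a model with categorical visit. Test the other visit at 0.05 only if the first is significant. Label the trend-over-time model supportive. The sponsor chooses which visit comes first.

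This changes wording only and leaves 58/116/128/169 as they are. The cost is that a confirmatory claim at the second visit depends on the first, so its power is the joint figure of about 66-71% under the plan's assumptions.

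If the sponsor prefers to require both visits, the article should say so and restate power as about 66-71% under its assumptions. If either visit is to count, splitting alpha to 0.025 per visit would need 70 per group for power 0.80 at each: 140 × 1.1 = 154, and 154/0.76 = 202.6, so 203 recruited. At the planned 58 per group, power per visit would be 0.71.

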#### School staff outcomes

These will be measured using a specifically designed questionnaire, based on those previously used by this research team [58]. This will be administered prior to the beginning of each school’s involvement in the study and at the end of the intervention period. If a staff member leaves the school before the end of the study they will be asked to complete the questionnaire before their departure. The questionnaire will assess attitudes, confidence; perceived skill and changes in practice.

All outcome data will de-identified and stored on a password-protected database located on a secure server housed by Orygen Youth Health Research Centre.

### Randomisation/treatment allocation

Participants (n = 170) will be recruited via each school’s student wellbeing coordinator. Once written consent is obtained from a potential participant, a baseline assessment will be conducted to ascertain his or her eligibility. The study coordinator (JR) will randomise eligible participants into either the treatment or control group using a randomisation list prepared by an independent statistician. The randomisation list (generated using random number generator computer software) is stratified by school and is incorporated into an online randomisation computer program. Immediately after each randomisation, the relevant school wellbeing staff member will be automatically notified of treatment allocation via email. They will then administer the appropriate treatment to the participant.

### Blinding and treatment fidelity

Because of the nature of the intervention (i.e. it is to be delivered by school staff) it is not possible for school staff to be blind to intervention. In addition, the study coordinator (JR) and the two study psychologists (SH and SB) will remain unblinded in order that randomisation can be conducted and to enable the website to be moderated. However the research assistants conducting outcome assessments and the statistician conducting the analysis will remain blinded to treatment allocation until study completion.

With regard to treatment fidelity, a study manual has been developed to facilitate this across sites. However it is acknowledged that the same school staff will be administering both the treatment and control interventions to students. Therefore there is the possibility of some contamination, in terms of school wellbeing staff incorporating some of the techniques from the CBT program into their work with students allocated to the control condition. However we consider this to be unlikely. Although school staff will be responsible for administering the program, they will not be required to supervise the student closely whilst they watch the program. Rather their role will be to set up appointments with the students, to remain in the vicinity whilst each module is completed, and to check the suicidal ideation screen at the end of each module. However in order to assess this we will ask all school wellbeing staff to complete a short checklist at the end of each session with a Reframe-IT student that will record the length and content of each session.

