#### Protocols and supervision

Clear and detailed safety protocols have been developed for this study detailing how undue risk will be determined and how the research team will respond. The research assistants will receive training in the administration of the measures and in the assessment of suicide risk. The research assistant will make contact with the school wellbeing staff member once each assessment is completed. If the research assistant and the school are concerned about the participant the project coordinator will be informed and, where necessary, an immediate referral will be made to an appropriate service. Fortnightly supervision meetings with the research therapist and the clinical psychologist will be held, during which all cases will be presented and any diagnostic and/or risk issues discussed.

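### Outcome assessors are promised to stay blinded, yet the plan has them administer, before the 22-week CDRS-R rating, a questionnaire on a program that only one arm receives

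*Protocol article*

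**What the plan says.** All references are to the protocol article.

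- **Who is blind.** The section Blinding and treatment fidelity states that "the research assistants conducting outcome assessments and the statistician conducting the analysis will remain blinded to treatment allocation until study completion".
- **Who is not.** The same section says of school personnel that "it is not possible for school staff to be blind to intervention", and that the coordinator and the two study psychologists "will remain unblinded in order that randomisation can be conducted and to enable the website to be moderated". The section Randomisation/treatment allocation adds that the school staff member is emailed each allocation.
- **The questionnaire.** Under Outcome measurements, Student outcomes, the research assistant gives every measure at every time point, "with the exception of the evaluation questionnaire, which is only administered post-intervention". Its content is described later in that section: "Participant satisfaction and the extent to which they find the program acceptable will be measured using a specifically designed measure at post-intervention".
- **Contact with schools.** Under Protocols and supervision: "The research assistant will make contact with the school wellbeing staff member once each assessment is completed".
- **Supervision.** The same paragraph continues: "Fortnightly supervision meetings with the research therapist and the clinical psychologist will be held, during which all cases will be presented".

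**The concern.** The blinding statement has no qualification, but procedures elsewhere in the article do not fit it. A questionnaire about the program has meaning only for students who had the program, and the control arm receives treatment as usual alone. An assistant who administers it at 10 weeks can learn a student's arm while a further interview with that student is still to come.

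At stake is the CDRS-R, which is scored by the interviewer. Depressive symptoms are the second of the trial's stated aims. An assessor who knows or suspects the arm may, without intending it, score intervention students as more improved. A report that described this outcome as blindly assessed could then claim more than the procedures deliver.

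**Working it through.** No figure in the plan bears on this point, so the check sets the procedures side by side.

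**1. Does the exception take the questionnaire away from the assistant?** No. The sentence has the research assistant administer each measure at each time point and then makes an exception for the evaluation questionnaire because it is given only once. The exception concerns timing, not who administers it.

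**2. Does the questionnaire reveal the arm?** It asks about satisfaction with the program and its acceptability. The section Control intervention gives controls treatment as usual only. If only intervention students receive the questionnaire, being given it marks the arm. If everyone receives it, controls have no program to rate. Either way its content is specific to one arm.

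**3. When does exposure matter?** Exposure matters only if a rating of that student is still to come.

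| Assessment | Arm assigned? | Program questionnaire? | Staff contact afterwards? | CDRS-R rating open to influence |
|---|---|---|---|---|
| Baseline | No (it precedes randomisation) | No | Yes | None: no arm to disclose |
| 10 weeks | Yes | Yes | Yes | 22 weeks; also 10 weeks if the questionnaire precedes the interview |
| 22 weeks (10 + 12) | Yes | No | Yes | None for that student |

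The 10-week visit is therefore the critical one. The order of questionnaire and interview at that visit is not given.

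**4. Which outcome is exposed?**
- The CDRS-R has 17 items. The interviewer scores 14 from the student's answers and 3 from observed non-verbal behaviour (14 + 3 = 17). Every item passes through the assessor's judgement.
- The SIQ is a 30-item self-report, completed online by students who know what they received. Assessor blinding protects it little in any case.

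**5. How many students could be involved?** The planned sample is 170. Assuming equal allocation, which the article does not state, 170 / 2 = 85 are in the intervention arm. At the plan's 24% dropout, 85 × (1 − 0.24) = 64.6, or about 65, remain in follow-up. This counts retained intervention students, on whom the questionnaire route could act. It is not a count of unblindings.

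**The case against.** The strongest reply is that no procedure hands the allocation to the assistant.

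- **Online completion.** All outcome measures except the CDRS-R are given online, so the assistant need not see the questionnaire or its answers. This stands as a softening. It does not settle the matter, because the assistant is still the person assigned to administer it, and nothing in the article separates the assistant from it.
- **A different rater at 22 weeks.** There are two research assistants, so the later interview may fall to the other one. This is possible, but the article does not provide for it, and with only two assistants it is limited protection.
- **Contact with school staff serves safety.** The paragraph is about concern for the student, and no disclosure of arm is described. This also stands. The contact is an opportunity for disclosure, not a disclosure, and as the table shows only the 10-week contact can matter. It supports the point but would not carry it alone.
- **Supervision.** The article does not say that the assistants attend the fortnightly meetings. Their attendance is a reasonable inference, since the paragraph deals with their training and conduct, but it remains an inference. Presenting a case to someone who knows the arm does not in itself reveal it to the presenter. This is a likely further route, not an established one.
- **A condensed article.** Instructions against disclosure may well be in the full protocol or study manual, and their absence here is no fault. The point rests on what the article does state: the blinded assessor is assigned an instrument specific to one arm.

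**Conclusion.** The point holds for the research assistants. Followed as written, the plan puts allocation within the assessors' reach at 10 weeks, which does not fit the promise of blinding until study completion. The reach is modest: one secondary outcome, the CDRS-R, mainly at 22 weeks, and at 10 weeks only if the questionnaire comes first. The amount of bias cannot be estimated from the article. The conclusion assumes that the assistant's role in administering the questionnaire is real, and that the assistant who does so, or the other after hearing of it, rates the 22-week interview.

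Two stronger readings are tempting, and the article does not support them.

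- **That the statistician is also exposed.** A reader might infer this from the sentence "Interim analysis will be conducted twice yearly, or upon request to facilitate the safety monitoring of the project". But no section gives the analysing statistician the allocation, and a separate, independent statistician prepares the randomisation list. The sentence ties the interim work to safety monitoring and does not say who does it or whether it is by arm. Any figure for an inflated error rate would need a repeated testing rule that appears nowhere in the article.
- **That the primary outcome is compromised.** Nothing says that the assistant sits beside students while they complete the SIQ, and the measure does not depend on the assessor's judgement.

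**What to change.** Amend the student outcomes section so that the evaluation questionnaire is delivered online, to intervention students only, after the 10-week CDRS-R score has been locked and without the research assistant. The assistants should not see the responses before the 22-week ratings are complete.

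Add one sentence to the blinding section asking school staff and supervisors not to disclose arm to the research assistants. The handover of risk information between assistants, school staff and the study team stays exactly as it is.

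The cost is a small separate online step and a few lines of text. Completion of the questionnaire may be slightly lower outside the assessment session, but it is an acceptability measure and not an efficacy outcome.
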